## Abstract

**Background:**

Up to a third of stroke patients and patients with traumatic brain injury suffer from insomnia, including problems to fall asleep or stay asleep at night. Insomnia may exacerbate other brain damage-related problems, for example regarding cognitive functioning and emotional well-being; may lead to poorer quality of life; and may complicate recovery processes. Cognitive behavioral therapy for insomnia, delivered face-to-face or online, is found to be effective in the general population. However, despite the high prevalence and serious consequences of insomnia following acquired brain injury, studies on the efficacy of face-to-face cognitive behavioral treatment in this population are scarce, and this applies even more for studies on online cognitive behavioral therapy. Therefore, this study aims to evaluate the efficacy of a newly developed guided online cognitive behavioral therapy for insomnia following acquired brain injury.

**Methods:**

A multicenter, prospective, randomized, open-label, blinded end point study (PROBE) will be conducted, in which 48 patients diagnosed with stroke or traumatic brain injury and insomnia will be randomly allocated to the online cognitive behavioral therapy for insomnia treatment group or the treatment as usual group. The treatment consists of 6 online cognitive behavioral therapy sessions given on a weekly basis and personalized feedback after each session, combined with 2 face-to-face sessions. Outcomes will be assessed at baseline, immediately after the intervention period and at 6-week follow-up. The primary outcome is the insomnia severity assessed with the Insomnia Severity Index. Secondary outcome measures include sleep quality, sleep features derived from the sleep diary, fatigue, anxiety and depression, subjective cognitive functioning, and societal participation.

**Discussion:**

This study will provide insight on the efficacy of online cognitive behavioral therapy for insomnia following stroke and traumatic brain injury.

**Trial registration:**

Netherlands Trial Register NTR7082. Registered on 12 March 2018.

## Background

There is increasing awareness that sleep disorders following acquired brain injury are a serious problem and therefore need attention. These sleep disorders include sleep apnea, circadian rhythm disturbances, excessive daytime sleepiness, increased need for sleep, and insomnia [1–3]. The latter is most commonly reported. Complaints include trouble falling asleep, staying asleep, or waking up early and are accompanied by daytime complaints. Up to a third of stroke patients [4] and patients with traumatic brain injury (TBI) [2] meet DSM-IV criteria for insomnia disorder (ID), which is three times more than the 10% of the general population that suffers from ID [5]. Insomnia may exacerbate other brain damage-related problems, for example regarding cognitive functioning and emotional well-being; may lead to poorer quality of life; and may complicate recovery processes [2, 4, 6]. The treatment of insomnia should therefore be an important part of rehabilitation after acquired brain injury.

Numerous randomized controlled trials have shown that cognitive behavior therapy for insomnia (CBT-I) is an effective treatment for insomnia in otherwise healthy people, as well as in several populations with insomnia comorbid with another disorder [7–9]. A problem with implementation of CBT-I on a large scale is the lack of skilled therapists, limiting access to treatment. Online versions of CBT-I have been developed to reach a larger group of patients with insomnia. Recent reviews show that Internet-delivered CBT-I is effective in improving sleep in adults with insomnia [10, 11].

Despite the high prevalence and serious consequences of insomnia in stroke patients or patients with TBI, studies examining CBT-I following acquired brain injury are scarce. To date, CBT-I was examined in two studies concerning stroke patients [12, 13] and five studies concerning patients with mild to severe TBI [14–18]. The CBT-I protocol applied in the studies consisted of four to eight weekly sessions, combining cognitive and behavioral techniques including stimulus control, sleep restriction, cognitive therapy, and sleep hygiene education. CBT-I was adapted to brain injury patients by adding information on factors that could contribute to insomnia specifically after brain injury. CBT-I was administered online in one study [18] and face-to-face in the other six studies. Six out of these seven studies found significant improvement on sleep outcomes [12–14, 16–18] and four of these studies found significant improvement on secondary outcomes as depression and fatigue [12, 14, 15, 17]. Only three studies were randomized controlled trials, of which two compared CBT-I with treatment as usual [12, 14] and one compared CBT-I with a placebo condition (online education only) [18]. Furthermore, only three out of the seven studies—and none of the randomized controlled trials—formally assessed a diagnosis of ID as inclusion criterion [13, 16, 17]. More randomized controlled trials using formal diagnosis of ID are needed in order to reach a well-founded conclusion on the efficacy of CBT-I in patients with stroke or TBI.

For the present study, we developed an online eHealth CBT-I (eCBT-I) (see Table 1 for more details). Not only is eHealth easier to access and probably more cost-effective, it also has more benefits for patients, such as the opportunity to reread information and the freedom to follow treatment at their own time, place, and pace. The present study will compare eCBT-I with treatment as usual in patients with stroke or TBI to evaluate the added value on top of standard care. Treatment as usual does not address sleep.

**Table 1 Tab1:** Overview of online cognitive behavioral therapy for insomnia (eCBT-I)

Week 1:	­ Face to face session to provide information about the eHealth treatment and to optimize motivation for treatment
	­ Start of online session 1: psychoeducation on sleep, the different sleep stages, and sleep disorders following acquired brain injury and their consequences in daily life. Homework assignment: map personal sleep problems and their consequences for daily life together with coping so far: what was helpful and what was not?
	­ Start with a daily sleep diary, which will be continued throughout the treatment.
Week 2:	­ Online session 2: setting personal goals for treatment, information about sleep hygiene. Homework assignment: write down sub goals to improve sleep hygiene for the following week.
Week 3:	­ Second face- to- face session to evaluate the personal goals for treatment
	­ Online session 3: information on the relation between stress and sleep and different relaxation techniques. Homework assignment: practice of these relaxation techniques the following week.
Week 4:	­ Online session 4: information on the circadian clock which is entrained by light and temperature and the influence of activation on daytime sleepiness. Homework assignment: to balance activities and relaxation or to be more active during daytime.
Week 5:	­ Online session 5: different cognitive techniques, such as mindfulness and cognitive restructuring. Homework assignment: address and change unhelpful cognitive beliefs.
Week 6:	­ Online session 6: consolidation and relapse prevention.

### Objectives

The objectives of this study are:
To evaluate the efficacy of eCBT-I in reducing insomnia severity posttreatment and at 6-week follow-up in patients with insomnia following a stroke or TBI, as compared to treatment as usual (TAU)To evaluate the efficacy of the eCBT-I in reducing complaints about fatigue, cognitive functioning, emotional well-being, and societal participation posttreatment and at 6-week follow-up compared to TAUTo explore whether treatment efficacies vary with severity of insomnia, with the severity and type of brain injury, and with the time since brain injury.

Our primary hypothesis is that eCBT-I will reduce insomnia posttreatment more than treatment as usual, compared to baseline. Our secondary hypotheses are that eCBT-I will improve fatigue, cognitive functioning, emotional well-being, and societal participation.

## Methods

### Study design

The randomized controlled trial (RCT) uses a multicenter, prospective, randomized, open-label, blinded end point study design (PROBE) [19] to compare eCBT-I with TAU. A total of 48 patients will be randomly assigned to the eCBT-I or TAU group. Assessment will be performed at baseline (T1), 1 week after the 6-week intervention period (T2), and after 6-week follow-up (T3). The total duration of participation is 14 weeks. See Fig. 1 for a flowchart.

**Fig. 1 Fig1:**
[figure not shown]
Flowchart of study. eCBT-I, online cognitive behavioral therapy for insomnia; TAU, treatment as usual

### Recruitment, randomization, blinding, and treatment allocation

Participants will be recruited from five outpatient rehabilitation centers spread over the Netherlands (Heliomare Rehabilitation at Wijk aan Zee, Reade at Amsterdam, Rehabilitation Friesland at Beetsterzwaag, Basalt Rehabilitation at Delft and The Hague, and Adelante at Hoensbroek). Patients that are eligible based on the inclusion and exclusion criteria will be asked to participate. After informed consent is given, participants will complete the baseline measurement. Participants will then be randomly assigned to the eCBT-I or the TAU group. All participants will continue with standard rehabilitation care for various complaints, which do not specifically address insomnia (see Table 2). As complaints differ between persons, interventions differ as well. This care can include psychotherapy aimed at mood or other psychopathology, therapy aimed at cognitive functioning, physiotherapy, fitness, occupational therapy, and social work. The therapy dosage depends on different needs and capacity of participants. The variation in rehabilitation care between participants is expected to be similar for both groups and will be registered at follow-up by their clinicians. The TAU group will only receive standard rehabilitation care and can receive the eCBT-I after the study period. Participants can leave the study at any time for any reason without consequences. In case of withdrawal, participants will be asked to still do the measurements to control for attrition bias and a new patient will be included in accordance with the procedure. The measurements and intervention are not likely to have adverse consequences. Randomization will be done by a research randomizer program (www.randomizer.org) using permuted blocks to balance participants equal to both groups within centers. Treatment assignment is blinded, as researcher assistants, clinicians, and participants are unaware of number of included participants per center and not informed of this randomization procedure. Treatment allocation is not blinded for therapist and participant, as the nature of cognitive behavioral therapy does not permit blinding, but will be concealed until participants are recruited and baseline measurements are finished. Outcome assessment is self-reported and therefore not blinded for participant, but potential assessment bias of clinician or data collector on outcomes is excluded. Data collector is blinded for treatment allocation as well. Research assistant responsible for data input is blinded. See Table 3 for an overview of all measurements.

**Table 2 Tab2:** Overview of treatment as usual (TAU)

TAU is standard rehabilitation care for various complaints, which do not specifically address insomnia. As complaints differ between persons, interventions differ as well.^a^ This care can include:	
	­ Neuropsychological assessment
	­ Psychotherapy aimed at mood or other psychopathology (online and/or face-to-face)
	­ Cognitive therapy
	­ Physiotherapy
	­ Fitness
	­ Occupational therapy
	­ Social work
	­ Vocational therapy

^a^Both groups will receive treatment as usual; dosage depends on their individual needs and capacity of participants. The variation in rehabilitation care between participants is expected to be similar for both groups and will be registered at follow up by their clinicians

**Table 3 Tab3:** Assessment measures and time-points

	Enrolment	Baseline T1	Posttreatment T2	Follow-up T3
Eligibility screening	X			
Stop bang questionnaire	X			
Informed consent	X			
ISI		X	X	X
PSQI		X	X	X
Sleep diary		X	X	X
DMFS		X	X	X
HADS		X	X	X
CFQ		X	X	X
USER-P		X	X	X
Questionnaire received treatment				X

Questionnaire “received treatment” collects information on given standard rehabilitation care (TAU) during study period, reported by their clinicians

*ISI* Insomnia Severity Index, *PSQI* Pittsburg Sleep Quality Index, *DMFS* Dutch Multifactor Fatigue Scale, *HADS* Hospital Anxiety and Depression Scale, *CFQ* Cognitive Failure Questionnaire; *USER-P* Utrecht Scale for Evaluation of Rehabilitation—Participation, *T1* week 1, *T2* week 7, *T3* week 14

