### Sample size calculation

Calculation of power and group size in a repeated measures design requires an estimate of the expected intraclass correlation coefficient (ICC, within subject correlation). We therefore resorted to a recent randomized trial of Dekker and colleagues (2020) on the effect of eCBT-I on ISI in people with insomnia. We used this intraclass correlation coefficient as indication of follow-up of ISI assessments across 6 weeks in our study population with acquired brain injury. That study reported an ICC of 0.54 for ISI assessments repeated across 6 weeks in 175 people suffering from insomnia without brain injury [33]. Calculation of power and group size moreover requires an estimate of the expected treatment effect size. Whereas treatment effects of eCBT-I are often reported to be of moderate to large size, we preferred to be somewhat conservative and expect a somewhat smaller than moderate effect in the population of TBI and stroke and therefore used *f* = 0.20. Calculation of the required sample size using G*Power [34] for ANOVA, with two repeated measures and ICC of 0.54, indicated that 48 completers would provide (2 × 24), at a significance of alpha = 0.05, sufficient power (1-beta = 0.80) for a minimal detectable time-by-group interaction effect of *f* = 0.20 (small to moderate).

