### Statistical analyses

Data analysis will be performed with SPSS 23 (IBM; Armonck, USA). Means and standard deviations of the demographic and injury-related variables and the clinical characteristics collected at baseline will be calculated. As normality assumptions may not be met with this small sample size, data distributions and all model assumptions will be checked for all analyses. If model assumptions are not met, data will either be transformed or analyzed using a non-parametric test, as appropriate. For data not normally distributed, median and interquartile range will be reported. Independent *T* tests will be used to check for an imbalance between groups. Nominal variables will be checked with *χ*^2^ tests and ordinal variable with the Mann-Whitney Test. Statistical significance will be set at a *p* value of 0.05. To accommodate likely occasional missing days, the repeated measures obtained by diaries will be analyzed with mixed effect models. The treatment effects will be examined using a repeated-measures ANOVA. In the case of significant baseline imbalance, post hoc analysis of covariance (ANCOVA) will be used on the change scores of the outcome measures with baseline scores as covariates. Intention-to-treat analyses will be conducted and presented as primary results. Additionally, a per-protocol analysis will be performed. Also, we will compare the eCBT-I and TAU group with regard to the percentage of participants who have improved (reduction ≥ 6 points on the ISI) and recovered (ISI < 10). We will use mixed effect regression models to explore whether treatment efficacy, i.e., the time-by-treatment effect, is modified by time since brain injury and by diagnosis (stroke versus TBI).

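### Randomisation is blocked within five centres, but no named analysis includes centre; the test is slightly conservative if centres differ in ISI change

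*Protocol article*

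**What the plan says.** In the protocol article, the section Recruitment, randomization, blinding, and treatment allocation states: "Participants will be recruited from five outpatient rehabilitation centers spread over the Netherlands". Allocation is generated "using permuted blocks to balance participants equal to both groups within centers". Centre is the only stratification factor named, and the block size is not given.

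The section Statistical analyses sets out four pieces of modelling:

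- Main comparison: "The treatment effects will be examined using a repeated-measures ANOVA".
- If baseline imbalance is significant: "post hoc analysis of covariance (ANCOVA) will be used on the change scores of the outcome measures with baseline scores as covariates".
- Sleep diary: "the repeated measures obtained by diaries will be analyzed with mixed effect models".
- Effect modification: mixed models with time since injury and diagnosis as modifiers.

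Centre is a term in none of these. It does not enter the Sample size calculation either, which is based on a time-by-group interaction with two measures.

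**The concern.** Blocking within centre makes the arms nearly equal in size in every centre. Differences between centres then largely drop out of the treatment contrast, and its true variance falls. A model without centre does not know this. It leaves the between-centre variation in the residual and reports a standard error that is too large for the design. The confidence interval is then wider than it need be, the test rejects less often than its nominal 5%, and part of the precision gained by stratifying is not realised. With 24 per arm and planned power only just above 80%, it is worth asking how much is lost.

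**Working it through.** **1. Reproduce the planned sample size.** Inputs from the Sample size calculation: f = 0.20, N = 48, m = 2 measures, within-subject correlation 0.54, alpha 0.05.

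- Noncentrality: λ = f²·N·m/(1 − ρ) = 0.04 × 48 × 2/0.46 = 8.348.
- With 1 and 46 df, power is 0.807. At N = 46 it is 0.790. So 48 is the smallest even N that reaches 0.80, and the stated figure reproduces.
- Standardised difference in change implied by this effect: √(4λ/N) = √(4 × 8.348/48) = 0.834.

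**2. Which centre differences matter.** With two measures, the time-by-group test is the comparison of T2 − T1 between arms. A centre effect on ISI level is the same at T1 and T2 and subtracts out. As a check, a simulated level effect worth 30% of outcome variance gave a type I error of 4.8% and a ratio of model to true standard error of 1.01, that is, no mismatch. Only centre differences in change remain.

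**3. Size of the mismatch.** Let s be the centre share of change-score variance. With exact balance within centres and many centres, the model's variance is too large by the factor 1/(1 − s). The standard error is then too large by 1/√(1 − s), which is 1.026 at s = 0.05 and 1.054 at s = 0.10. This overstates the excess here, because there are only five centres and incomplete blocks leave some imbalance.

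The change score was therefore simulated with unit variance and a true difference of 0 or 0.834. Assumptions not in the article: centre sizes 10/10/10/10/8, block size 4, and the values of s. Each scenario had 8,000 runs, analysed without centre and with centre as a fixed factor.

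| Assumed s | Model SE without centre | True SE | Type I error, without / with centre | Power, without / with centre |
|---|---|---|---|---|
| 0 | 0.287 | 0.289–0.290 | 5.0% / 5.1% | 80.3% / 80.0% |
| 0.05 | 0.286 | 0.279–0.283 | 4.5% / 5.1% | 81.7% / 82.3% |
| 0.10 | 0.285–0.286 | 0.276 | 4.1% / 5.0% | 82.4% / 84.2% |
| 0.20 | 0.281–0.282 | 0.259–0.263 | 3.4% / 5.1% | 83.8% / 88.0% |

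The Monte Carlo standard error of a 5% rejection rate is √(0.05 × 0.95/8000) = 0.24 percentage points. The row for 0.05 is therefore hard to tell from no effect; allowing for this, the range there is about 0–3% for the standard error and 4.5–4.9% for type I error. At 0.10 the excess is 0.2857/0.2761 = 1.035 and 0.2851/0.2758 = 1.034, or 3–4%. At 0.20 it is about 7–8%.

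**4. Price of fitting centre.** Four further degrees of freedom (46 to 42) at the same λ take power from 0.807 to 0.806.

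**The case against.** The strongest reply is that this rests on silence. The article condenses a fuller document, nowhere says that centre will be left out, and model terms are commonly left to an analysis plan that is not shown. That limits certainty, and a centre term may exist elsewhere. But the section goes beyond pointing to another document: it names the main model, the fallback covariates and the effect modifiers. Leaving the one stratification factor out of all of them is open to comment. It is fair to add that the covariates are listed only for a conditional, post hoc ANCOVA.

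Three further objections stand and limit the point:

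- A reader might infer that the standard errors are wrong whatever the data show. They are not. Differences in level cancel, and with no centre difference in change there is no mismatch.
- A reader might take the article's remarks on variable usual care as evidence that centres differ. Those remarks describe variation between persons, and the care does not specifically address insomnia. Centre differences in ISI change are plausible but are not documented.
- A reader might infer that the benefit of stratifying is lost. Only part of it is. Balance within centres lowers the true variance whichever model is fitted. In the table, power without centre rises from 80.3% to 83.8% as the centre share grows.

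**Conclusion.** The point holds as a minor one. The design is stratified by centre and the named analyses are not. The consequence depends on an unknown, the centre share of change-score variance. At an assumed 0.05 it is barely visible. At 0.10 it costs about 1 point of type I error below nominal and about 2 points of power; at 0.20, about 1.6 and 4 points. These sizes also rest on the assumed centre sizes and block size.

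The error runs in one direction only: intervals too wide, tests too cautious. Nothing here makes a false-positive claim more likely, and the required 48 completers do not change.

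**What to change.** State in the analysis plan that centre, as the randomisation stratum, enters the primary ISI analysis and the analyses of the secondary scales. In the repeated-measures ANOVA this must be a centre-by-time term, since a centre main effect alone does not touch the time-by-group test. In the ANCOVA on change, a centre factor is enough. Add a rule for pooling very small centres, fixed before unblinding, so that the choice cannot depend on the results. If centre is to be left out, say so and give the reason.

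The cost is a change of wording and 4 degrees of freedom. No extra participants or data are needed.

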### Eligibility criteria

Participants are eligible for inclusion if diagnosed with stroke or TBI and insomnia disorder according to DSM-5 criteria. Furthermore, they should be aged 18 or older and capable of using the Internet. Exclusion criteria are untreated sleep apnea, current or expected treatment with a main focus on fatigue or sleep during the study, unstable medication regiments, use of medication with insomnia as side effect, alcohol or drug abuse, and a major untreated or unstable medical or psychiatric condition. Users of sleep medication will be encouraged to finish medication before enrolment or to keep intake stable during the study period. Depending on type and dosage of medication, the physician will determine the period needed to exclude the influence of finishing sleep-related medication on the outcome measures.

